### E.2.3. Facility Demographics

A variety of facility-level demographic data will be collected in order to assess comparability between control and intervention facilities. These will include:

- a) Geographic location (rural versus urban)
- b) Size (beds)
- c) Skilled nursing services provided (e.g., parenteral therapy, wound care, etc)
- d) Ratio of skilled to domiciliary care beds
- e) Resident complexity (Resource utilization group [RUG])
- f) Staffing ratios (registered nurse [RN], licensed practical nurse [LPN], certified nursing assistant [CNA])
- g) Staff turnover (RN, LPN, CNA)
- h) Existing facility antibiotic stewardship structure and process
- i) Organizational culture
- j) Nursing home quality measures

### **E.3. Data Collection Procedures**

#### **E.3.1. Primary Outcome Measures**

Participating NHs will submit data on the number of urine cultures and antibiotic starts via a web-based portal on a monthly basis.

#### **E.3.2. Secondary Outcome Measures**

Participating NHs will submit data on the number of urine cultures and antibiotic starts meeting Wisconsin appropriateness criteria [cite] via a web-based portal on a monthly basis. The Wisconsin appropriateness criteria [cite] require residents to either exhibit symptoms that localize to the urinary tract (e.g., dysuria, frequency) or systemic signs of infection (e.g., fever, hypotension, etc.) in the absence of another obvious source of infection.

The research team will obtain aggregate data on antibiotic prescriptions from the facility consultant pharmacy in order to determine days of antibiotic therapy per 1,000 resident-days as well as the number of fluoroquinolone starts and days of fluoroquinolone antibiotic therapy.

The research team will obtain aggregate data on urine culture results to determine the rates of urine culture resistance in study nursing homes. *Clostridium difficile* results at a facility level will be obtained in a similar manner.

Facilities will be asked to provide their aggregate resident transfer and mortality data on a monthly basis.

#### **E.3.3. Facility Demographics**

A facility demographics survey will be employed to collect information on study NH size, staffing levels, and types of skilled nursing services provided, etc. The Certification and Survey Provider Enhanced Reporting (CASPER) database, a Center for Medicaid and Medicare Services database that provides information about nursing home demographics and selected quality indicators, will be accessed to determine study nursing home staff turnover, aggregate measures of resident complexity and facility F-tag deficiencies (F-tag 329 [inappropriate medication use] and 441 [infection control]). A survey instrument developed by the research team [cite] will be used to characterize each facility's existing antibiotic stewardship structure and process. Another survey instrument developed by the research team [cite] will be employed to assess each facility's organizational culture. We will collect data on the number and the percentage of residents with UTI, as well as on the prevalence of UTI infections and other infections using

the CHSRA/DHS Nursing Home Scorecard. This scorecard, which is being developed by the UW Center for Health Systems Research and Analysis (CHSRA), provides trends across a wide array of resident level outcomes for Wisconsin Nursing Homes. It also includes comparisons to peer and NHs across the state. The scorecard will be used to report changes in these outcomes.

#### **E.4. Data Analyses**

Generalized estimating equations using segmented regression and a Poisson distribution accounting for clustering by facility will be employed to evaluate the two primary outcomes across all study sites in aggregate. Four estimates from these models will be evaluated: 1) the pre-intervention trend ( $\beta_1$ ); 2) the immediate change in the outcomes following the kickoff webinar ( $\beta_2$ ); 3) the difference between pre- and post-implementation trend ( $\beta_3$ ); and 4) the post-implementation outcome rate change ( $\beta_1 + \beta_3$ ). First and second order autocorrelation will be assessed using the Durbin-Watson statistic. Robust standard errors will be used to estimate variance. Similar generalized linear models will be fit to analyze secondary and safety outcomes. To assess the impact of enhanced implementation on the effectiveness of the toolkit, the segmented regression model developed will be extended to include a covariate for the study implementation arm (control arm = 0; intervention arm = 1). We will explore adding control variables into our models if significant imbalances in NH characteristics (e.g., size, staffing ratios) are identified in our preliminary analyses. Based on data previously collected by our group [6], the expected rate of UTI treatment is ~4.0 per 1,000 resident-days. Assuming implementation of the UTI Toolkit leads to at least a 15% reduction in the UTI treatment rate and the facility dropout rate is <25%, our study will have 90% power to detect a statistically significant difference of this magnitude.

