## II. Study Objectives

*Our long-term objective is to improve the quality and safety of antibiotic prescribing in Wisconsin NHs.*

The objective of the current project, which is a critical step in the pursuit of our long-term objective, is to identify effective strategies for supporting the implementation of antibiotic stewardship interventions in NHs. We hypothesize that externally-facilitated implementation based on coaching and peer-to-peer learning will be associated with: (**hypothesis 1**) better adoption of the Wisconsin UTI Improvement Toolkit and (**hypothesis 2**) reduced rates of inappropriate antibiotic use as compared to a usual implementation approach that relies predominantly on internal improvement resources available in NHs. We base these hypotheses on studies demonstrating more effective uptake of evidence-based practices with coaching [19-22] and peer-to-peer learning [23-25] in other healthcare settings, particularly resource-limited settings. A preliminary analysis of qualitative data collected from another of the PI's research projects (Agency for Healthcare Research and Quality 1R18 HS022465-01) indicates that clinical coaching is helping champions in study NHs identify barriers to change and develop more effective strategies for overcoming these barriers.

The primary study objectives are to assess the overall impact of the UTI Improvement Toolkit on antibiotic utilization and determine the extent to which effects vary by the implementation approach employed. We will achieve these two objectives through the following specific aims:

**Specific Aim 1: Evaluate the impact of the Wisconsin UTI Improvement Toolkit on antibiotic prescribing for UTI in Wisconsin NHs.**

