### **III. Study Methods**

#### **A. Overall Study Design and plan**

We will introduce the Wisconsin UTI Improvement Toolkit (see Section III.B. Wisconsin UTI Improvement Toolkit) in 20 Wisconsin NHs and assess its impact on antibiotic utilization using segmented regression. Two different implementation strategies (see Section III.C. Study Arms) will be employed during the introduction of the Wisconsin UTI Improvement Toolkit in study NHs using a hybrid type 2 effectiveness-implementation study design in which half of the NHs will be randomized to usual (internally-driven) implementation with the other half randomized to externally-facilitated implementation based on coaching and peer-to-peer learning. The effects of the two implementation approaches will be assessed using a mixed methods approach.

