##### **C.2. Intervention Arm: Externally-facilitated implementation**

NHs randomized to the externally-facilitated arm will attend the same kickoff meetings and have access to the same online resources as the control arm but will also be assigned a clinical coach and will have the opportunity to participate in a series of hosted peer-to-peer learning opportunities. The clinical coach will meet regularly with NH staff to guide the facility through implementation of the Wisconsin UTI Improvement Toolkit. Coach supports will occur during a site visit and individual coaching calls.

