### **C.2.4. Enhanced Feedback Reports**

Intervention NHs will be able to track their data using the web-based tracking tool that will be accessible by the control NHs. However, the feedback reports made available to intervention NHs will include information on the performance of other participating NHs (in aggregate) allowing the intervention NHs to trend their own data and benchmark themselves against their peers.

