### E. Study Outcomes

#### E.1. Overview

While the individual components of the Wisconsin UTI Improvement Toolkit are evidence-based, their combined effects on antibiotic prescribing are not known. We will assess the combined effects of the toolkit by comparing UTI treatment rates in study NHs before and after implementation of the toolkit using segmented regression methods. A number of data measures will be employed during this study.

| Focus Area                  | Domain                 | Measure(s)                                             | Data Source              |
|-----------------------------|------------------------|--------------------------------------------------------|--------------------------|
| Nursing Home Level Measures | Facility demographics  | Facility demographics (location, size, services, etc.) | UW NH Org Profile        |
|                             |                        | Resident characteristics (%post-acute, payer, etc.)    | CASPER database          |
|                             |                        | Nursing staffing levels (CNA, LPN, RN)                 |                          |
|                             |                        | Nursing retention measures                             |                          |
|                             | Work system            | People, tools, tasks, environment                      | Interviews & observation |
|                             |                        | Process and information flow maps                      |                          |
|                             |                        | ASP Structure and Process                              | UW ASP Survey            |
|                             | Organizational culture | Readiness for change                                   | UW organizational survey |
|                             |                        | Management support of frontline staff                  |                          |
|                             |                        | Perceived capacity to sustain change                   |                          |
| NH Level Measure            | Reach                  | # of NHs adopting the UTI toolkit with fidelity        | Interviews and surveys   |
|                             |                        | AS & DOT for UTI per 1,000 resident-days               | Facility supplied        |

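### The Aim 1 estimate averages the toolkit's effect over two implementation strategies, and the planned 0/1 arm covariate cannot show how the change divides between them

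*Protocol*

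**What the plan says.** Section III.A introduces the toolkit "in 20 Wisconsin NHs and assess its impact on antibiotic utilization using segmented regression", and "half of the NHs will be randomized to usual (internally-driven) implementation with the other half randomized to externally-facilitated implementation". Homes in the second group attend the same kickoff meetings and have the same online resources, but "will also be assigned a clinical coach and will have the opportunity to participate in a series of hosted peer-to-peer learning opportunities" (C.2). Their feedback reports also show how other participating homes perform (C.2.4). The appendix describes the toolkit as six modules; the coach, the peer meetings and the peer benchmark are not among them.

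Specific Aim 1 is to "Evaluate the impact of the Wisconsin UTI Improvement Toolkit on antibiotic prescribing for UTI in Wisconsin NHs". Section II, just before the aims, calls this the overall impact and names variation by implementation approach as the other primary objective. Section E.1 states: "We will assess the combined effects of the toolkit by comparing UTI treatment rates in study NHs before and after implementation of the toolkit". Section E.4 says that the Poisson segmented regression "will be employed to evaluate the two primary outcomes across all study sites in aggregate" and lists four estimates: the pre-kickoff trend, the immediate change, the change in trend and the post-kickoff trend. None is specific to an arm.

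For the arm question, E.4 and F.5 extend this model with one covariate coded 0 for control and 1 for intervention. F.1 adds a comparison of arms by generalized linear mixed models, but Section F is marked as still being developed. The sizing statement in E.4 attributes a 15% reduction to implementation of the toolkit and claims 90% power for it.

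**The concern.** In half of the homes the period after kickoff contains the toolkit plus external facilitation. Hypothesis 2 expects facilitation to reduce inappropriate antibiotic use further, so the protocol itself expects the two halves to differ. The pooled change then says what happened on average under an even mix of strategies. E.1 and E.4 describe it simply as the toolkit's effect, and E.4 does not call it an average.

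What is at stake is interpretation. One pooled result is compatible with a toolkit that works equally well in both arms and with one that changes little without a coach. Telling these apart needs the before-after change in each arm, and the model extension as worded does not produce it.

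**Working it through.** **Inputs from the protocol.** 20 homes, half per arm (III.A); expected rate about 4.0 UTI treatments per 1,000 resident-days, 15% reduction (rate ratio 0.85), 90% power, facility dropout below 25% (all E.4); more than 50 beds per home (D.1.1).

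**Assumed, because the protocol does not give them.** Two-sided 5% level, resident-days per home, months per period, design effect, and the split of the effect between arms.

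**1. The plan's own 90%.** For a simple before-after log rate ratio without clustering, the baseline events needed are (1.960 + 1.282)² × (1 + 1/0.85) / (ln 0.85)² ≈ 866. At 4.0 per 1,000 this is about 216,000 resident-days per period, or about 9.5 months with 15 homes of 50 residents and 7.1 months with 20. Over 15 or 20 homes, 50 to 100 beds, 3 to 12 months and design effects of 1 to 4, power runs from 15% to over 99%. The 90% can be neither confirmed nor refuted, so it is taken at face value below.

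**2. What the pooled change contains.** Let RRc be the before-after rate ratio in control homes and F the further ratio due to facilitation. With equal resident-days and equal baseline rates in the arms:

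- Pooled RR = (RRc + RRc × F)/2 = RRc × (1 + F)/2.
- On the rate scale the pooled figure lies exactly halfway between the arms.
- On the log scale, the share of the facilitation effect carried is ln((1 + F)/2) / ln F. This is 0.494 for F = 0.95, 0.487 for 0.90, 0.480 for 0.85, 0.472 for 0.80 and 0.456 for 0.70.

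If facilitated homes hold a fraction w of resident-days, the share is ln(1 − w + wF) / ln F. With F = 0.8 it is 0.325 for w = 0.35 and 0.624 for w = 0.65.

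**3. What a pooled 15% reduction could mean.** RRc = 0.85 / ((1 + F)/2):

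| Assumed F | Control-arm RR |
|---|---|
| 1.0 | 0.850 |
| 0.9 | 0.895 |
| 0.8 | 0.944 |
| 0.7 | 1.000 |

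**4. Whether the planned covariate separates the arms.** Poisson segmented models were fitted to noise-free expected counts (assumed: 20 homes of 75 beds, 12 + 12 months, RRc = 0.95, F = 0.80, no trends).

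- No arm term: step = 0.855, which is (0.95 + 0.76)/2.
- Arm covariate only: step still 0.855. The arm ratio is 0.9026, which is (1 + 0.76)/(1 + 0.95), a blend of a period with no arm difference and a period with one.
- Arm interacting with baseline trend, level change and trend change: control step 0.95 and further facilitation ratio 0.80, both as put in.

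**5. Precision of one arm.** Taking the 90% at face value, halving the information gives power Φ(3.242/√2 − 1.960) = Φ(0.332) ≈ 0.63 for the same 15% effect.

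**The case against.** The strongest reply is that the pooled quantity is a declared target. Section II names the overall impact as the objective and variation by approach as its companion, and an all-site analysis matches that. The design is a hybrid type 2 study of one toolkit delivered in two ways. Coaching works by fitting toolkit practices into existing workflows, so an effect gained through fuller adoption can fairly count as toolkit impact. An arm comparison is also planned, and a separate analysis plan may contain the interaction terms.

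Most of this stands. A reader might infer that Aim 1 means the toolkit under usual implementation and that the pooled analysis is therefore wrong. No section says so. The control arm does not isolate the toolkit either, since those homes also get kickoff meetings, online resources and a tracking tool. A reader might also argue that later adopters will have no coach, so only the control arm matters. The protocol does not say this, and its stated purpose is to find effective strategies for supporting implementation.

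Two things remain. E.4 does not label the estimate as an average over strategies. And the arm extension that the protocol itself fixes, in both E.4 and F.5, is a single covariate, which does not yield before-after changes by arm.

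**Conclusion.** The pooled model is a valid answer to the overall-impact objective, and its place as the Aim 1 estimate need not change. It is not an estimate of the toolkit's effect under usual implementation and should not be read as one. If facilitation has an effect, the pooled figure includes roughly half of it. That share rests on equal resident-days and similar baseline rates and dropout in the two arms, and it moves with any imbalance. If facilitation has no effect, the issue has no consequence. The protocol gives no arm split, so the actual size is unknown. The firmer defect is that a lone 0/1 arm term cannot show whether the pooled change comes from the facilitated homes. This is a point of labelling and model specification, cheap to correct.

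**What to change.** In E.4:

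- Keep the all-site estimate as the Aim 1 overall impact, and state that it averages over the two implementation strategies.
- State that the 15% reduction and the 90% power refer to that average.
- Replace the lone arm covariate by one model with arm-by-level and arm-by-trend terms (including the baseline trend), and report each arm's level and trend changes beside the pooled estimate. Make the matching change in F.5.
- State that the pooled effect will not be attributed to the toolkit under usual implementation unless the control-arm estimate supports it.

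No new data are needed, and the same interaction terms serve the arm comparison in Aim 2. The cost is precision: each arm-specific estimate rests on about 10 homes, fewer after dropout, with power near 63% instead of 90% for the same 15% effect. These estimates should therefore be presented with intervals, and a non-significant control-arm result should not be read as no effect.

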## **D. Study Sites**

### **D.1. Overview**

20 Wisconsin NHs, purposively selected for their geographic location to achieve a balance between rural and urban facilities, will be selected for participation in this study. Our rationale for employing this sampling approach is that rural NHs are less likely to be members of a NH network and may have more limited access to improvement resources and expertise. This approach will enhance our capacity to identify barriers to implementation that will be encountered in NHs throughout Wisconsin and enhance future toolkit dissemination efforts.

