#### D.3. Randomization

Randomization will be computer generated and stratified based on geographic location (urban vs. rural) in block sizes of two.

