## F.5. Data Analyses

A mixed methods evaluation approach structured around the RE-AIM framework [32] will be employed in this aim. **Reach** is the percentage of NHs that adopt the Wisconsin UTI Improvement Toolkit with fidelity. To compare differences in toolkit **effectiveness** between the two implementation strategies, the segmented regression model that will be developed (see Section III.E.4) will be extended to include a covariate for the study implementation arm (control = 0; externally-facilitated = 1). **Adoption** will be assessed both quantitatively (differences between NHs in the two implementation arms will be assessed by survey items measuring organizational readiness for change, staff knowledge, attitudes and perceptions about the UTI toolkit) and qualitatively using a thematic approach [34] structured around System Engineering Initiative for Patient Safety (SEIPS) framework [35]. Differences in the extent of **implementation** in NHs randomized to the two approaches will be assessed by comparing responses to a UTI toolkit fidelity checklist and qualitatively through analyses of data collected during staff interviews that focus on the identification of implementation strategies and barriers. Short-term **maintenance** of the effectiveness outcomes will be assessed utilizing an approach developed by Drs. [name] and [name] [36]. To assess the impact of coaching, we will utilize the comparative conceptual framework proposed by Bond and Seneque [37] which suggests that organizational coaching occurs across one of five domains: managerial, consulting, mentoring, facilitating or coaching to classify the advice provided during the coaching interactions. Quantitative and qualitative data will be integrated in an attempt to explain implementation success and failures using a formal triangulation approach [38]. Coaching notes, interview transcripts with NH champions, and notes generated during hosted peer-to-peer learning sessions will be analyzed thematically to identify common barriers NHs encountered and strategies employed to overcome them as well as the types of coaching instruction that were most impactful on facility implementation efforts.

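### The arm comparison omits the urban/rural randomisation stratum, and the only covariate rule, adjustment after significant imbalance, would practically never bring it in

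*Protocol*

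**What the plan says.** - **Design.** Protocol III.D.1 describes "20 Wisconsin NHs, purposively selected for their geographic location to achieve a balance between rural and urban facilities". Under III.A, "half of the NHs will be randomized to usual (internally-driven) implementation with the other half randomized to externally-facilitated implementation", so about 10 homes per arm. III.D.3 states: "Randomization will be computer generated and stratified based on geographic location (urban vs. rural) in block sizes of two".
- **Arm model.** In III.E.4 the segmented regression is "extended to include a covariate for the study implementation arm (control arm = 0; intervention arm = 1"). III.F.5 repeats this: "extended to include a covariate for the study implementation arm (control = 0; externally-facilitated = 1"). III.F.1 mentions generalized linear mixed models for the same comparison. None of the three names the stratum.
- **Covariate rule.** III.E.4: "We will explore adding control variables into our models if significant imbalances in NH characteristics" are identified in preliminary analyses. Size and staffing ratios are the examples given.
- **Candidates.** III.E.2.3: "A variety of facility-level demographic data will be collected in order to assess comparability between control and intervention facilities". Ten items follow, (a) to (j). Item (a) is rural versus urban location.

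**The concern.** Two things sit badly together. The factor that restricted the randomisation does not appear in the model for the randomised comparison. The only way for a covariate to enter is an observed imbalance, which under correct randomisation is a chance event and has no link to how strongly the covariate predicts the outcome.

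What is at stake is the arm comparison of Aim 2, the only randomised contrast in the trial, which rests on 20 clusters. Its model would be settled only after the baseline data have been seen. If urban and rural homes differ in outcome, its standard error would also carry variation that the design had already balanced out.

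**Working it through.** **1. The plan's own figure.** The only power figure is 90% for a 15% reduction from 4.0 per 1,000 resident-days (III.E.4). It concerns the pooled pre/post effect. For 4.0 versus 3.4 with pure Poisson variation and two-sided 5%, the exposure needed per period is (1.960 + 1.282)² × (0.0040 + 0.0034) / 0.0006² ≈ 216,000 resident-days. The protocol gives no exposure, so the 90% can be neither confirmed nor refuted. It does not bear on the arm comparison.

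**2. How large a gap must be to count as significant.** Inputs: 10 versus 10 homes (III.A, III.D.1); two-sample t-test at 5% (assumed). Smallest significant observed gap = t(0.975; 18 df) × √(2/10) = 2.101 × 0.447 = 0.94 SD.

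**3. How often chance gaps arise.** The chance difference in means has SD √(2/10) = 0.447. P(|gap| > 0.5 SD) = 2 × [1 − Φ(0.5/0.447)] = 0.26 per characteristic. Only about 5% are flagged, so roughly (26 − 5)/26, or four in five, of those gaps go unflagged.

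**4. How often something is flagged by luck.** Nine items remain once location is set aside: 1 − 0.95⁹ = 0.37 if independent. Correlation among items lowers this. Testing staffing and turnover separately for three staff grades each raises the count to 13 and the figure to 1 − 0.95¹³ = 0.49. In simulation, a truly prognostic covariate was flagged about 5% of the time, like any other.

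**5. Whether the rule could admit the stratum.** Blocks of two within strata leave the arms within one home of each other in each stratum. Dropout does little to change this. Suppose 5 urban and 5 rural homes per arm, and the loss of four homes (the protocol assumes under 25% of 20), all urban and all from one arm. The split is then 5/5 versus 1/5, and the one-sided exact probability is [C(10,6) + 6 × C(10,5)] / C(16,6) = (210 + 1,512)/8,008 = 0.22.

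**6. What omission costs when the arm effect is a level term, as III.E.4 words it.** A Poisson segmented regression with cluster-robust standard errors was simulated for 20 homes. Exposure and between-home variation are assumed, because the protocol gives neither.

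| Urban/rural rate ratio | Arm SE without stratum | Arm SE with stratum |
|---|---|---|
| 1.5 | 0.168 | 0.138 |
| 2.0 | 0.211 | 0.140 |

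A hand check for two equal strata uses SE²(without) ≈ SE²(with) + (4/20) × (ln R / 2)².
- R = 1.5: √(0.0190 + 0.0082) = 0.165.
- R = 2.0: √(0.0196 + 0.0240) = 0.209.

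The reported SE is therefore about 22% (0.168/0.138) or 51% (0.211/0.140) larger than it need be.

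**7. Effect on error rates.** This is a simpler facility-level normal model: two strata of 10, within-stratum SD 1, true arm effect 1.2 SD, 20,000 runs.

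| Urban/rural gap (SD) | Type I error without stratum | Power without stratum |
|---|---|---|
| 0 | 0.050 | 0.72 |
| 0.5 | 0.046 | 0.70 |
| 1.0 | 0.027 | 0.62 |
| 1.5 | 0.016 | 0.52 |
| 2.0 | 0.005 | 0.38 |

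With the stratum, type I error is 0.048 to 0.053 and power 0.71 to 0.72 throughout. Testing for imbalance and then adjusting gave type I error of 0.038 to 0.053.

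**8. If the arm effect is estimated as arm×post.** A stratum main effect then gains nothing, because a time-constant level cancels within each home: SE 0.094 with or without it at a rate ratio of 1.5. If rural homes respond differently (assumed ratio 1.25 on the post-kickoff change), the SE stays at 0.111 with the main effect and falls to 0.097 only with stratum×post.

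**The case against.** **The omission is silence, and an analysis plan may fill it.** This is partly right. The protocol gives no closed covariate list, the SAP is not at hand, and Section III.F says its methods are still being developed. Silence alone would be no finding. But III.E.4 carries no such caveat, and it does state a rule for how covariates enter. That rule would need replacing whatever the SAP adds.

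**No test or threshold is named, and the wording is only exploratory.** True. Significance testing at 5% is the natural reading, not a stated one. A looser reading leaves more to discretion after the data are seen.

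**A stratum main effect may buy nothing.** This stands where the effect is arm×post (step 8), and it shapes the fix.

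**Stronger readings that a reader might infer, and that the documents do not support:**
- *That stratification was chosen because rural homes have fewer resources.* That reason appears in III.D.1 for the purposive sampling of sites. III.D.3 gives none, and no section says that location predicts culture or treatment rates.
- *That the chance of a false flag is 40%, from all ten items.* Location is balanced by design, so nine items is the right count.
- *That a 0.5 SD imbalance is caught only 18.5% of the time and a 0.8 SD one 39.5%.* Those are powers against a population difference, which randomisation rules out. What counts is the observed gap: flagged above about 0.94 SD, not below.

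**Conclusion.** The point holds in a limited form. The written covariate rule selects on chance: about a 37% probability of at least one flag among nine independent items, no flag for gaps below about 0.94 SD, and practically no route for the stratum. The model for the randomised comparison is therefore not fixed in advance. If urban and rural homes differ, that comparison is also conservative and less precise than the design allows.

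A reader might infer bias or an inflated false-positive rate. Neither follows: the stratum is balanced between arms, and the simulated type I error stays at or below about 5%. The pooled pre/post analysis and its 90% power are not affected.

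The size of the precision loss rests on assumed urban/rural differences, assumed exposure and simplified models. If location has no effect, the loss is nil (power 0.72 either way). The imbalance arithmetic assumes 10 versus 10 homes, 5% tests and independent items.

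**What to change.** Replace the covariate sentence in III.E.4, and align III.F.1 and III.F.5 with it:

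> All arm-comparison models include the urban/rural stratum in the same form as the arm term: as a main effect where the arm effect is a level contrast, and with its post-kickoff interaction (stratum×post) where the arm effect is estimated as arm×post. Covariates are not selected by tests of baseline imbalance; any further covariate is named in advance on prognostic grounds.

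The characteristics in III.E.2.3 can still be tabulated by arm as description. Location is already collected, so nothing new is needed from the homes. The price is one degree of freedom for the main effect, or two with the interaction. With 20 clusters that is not entirely free, but in the facility-level simulation the main effect cost almost no power when location was irrelevant (0.72 with or without it).
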